### Data processing

Data processing occurs in two stages: a **runtime** pipeline that drives real-time XR biofeedback during the experimental session, and a **post-session** pipeline that processes recorded data offline to compute objective outcome measures.

#### Runtime processing pipeline

The runtime pipeline is executed by the Unity application running as a standalone build on the Meta Quest 3 headset. Its purpose is to generate low-latency normalized EMG values for real-time visual feedback. Processing occurs across three stages.

##### Stage A — sensor hardware (Delsys Trigno Avanti)

Each Trigno Avanti sensor performs onboard EMG conditioning using a 20–450 Hz hardware band-pass filter before wireless transmission to the Trigno Research+ Base Station (SP-W02). The base station sends digitized EMG channels to the workstation, where they are ingested by QTM Software.

##### Stage B — QTM software (workstation)

QTM Software receives the EMG channels and 3D marker trajectories, synchronizes both streams using the shared TTL trigger, and packages them into real-time frames for streaming to Unity through the QTM SDK.

##### Stage C — Unity application (Meta Quest 3)

The Unity application polls QTM for EMG data over Wi-Fi. For each EMG channel, Unity computes RMS amplitude from the latest QTM analog sample packet, applies a 20-update rolling RMS window, and normalizes the resulting value by the corresponding MVIC reference to produce a %MVIC value. The six %MVIC values are then sent to the visualization controller: avatar muscle coloring, dynamic bar indicators, or live waveform graphs. The feedback is rendered in either VR or MR mode according to group allocation.

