### Equipment and instruments

The experimental setup will include an immersive display, motion-capture, EMG sensing, exercise, and computing components, as shown in Fig. 1.•**Immersive display:** The Meta Quest 3 headset (Meta Platforms, Inc., Menlo Park, CA, USA) will be used for both VR and MR conditions. It provides standalone operation, inside-out tracking, high-resolution display, and full-color passthrough for MR feedback.•**Motion capture:** Kinematic data will be captured using a Qualisys motion-capture system with 12 Arqus A5 and 2 Miqus video cameras arranged around an approximately 10.0 × 6.0 × 2.5 m capture volume. Cameras will be positioned approximately 2.9 m above the floor and angled inward/downward to maintain shoulder-marker visibility. Calibration will use an L-frame and T-wand, with a target residual error below 0.5 mm. Cameras will be synchronized at 300 Hz. Reflective markers will follow the Qualisys Sports Marker Set to compute joint angles, range of motion, velocity, and smoothness metrics.•**EMG:** EMG data will be collected using six Delsys Trigno Avanti wireless sensors (Delsys Inc., Natick, MA, USA; Model SP-W06) connected to a Trigno Research+ Base Station (Model SP-W02). EMG will be sampled at 1926 Hz using the 20–450 Hz bandwidth setting. EMG and motion-capture recordings will be synchronized using a hardware TTL synchronization signal generated by the Qualisys Camera Sync Unit.•**Exercise equipment:** Adjustable dumbbells (2–5 kg) and resistance bands of varying resistance levels will be used for exercise tasks and maximum voluntary isometric contraction (MVIC) calibration.•**Computing infrastructure:** Data acquisition, VR and MR application development, and real-time signal processing will run on a workstation with an Intel i9–11900K processor, NVIDIA RTX 3060 Ti 8 GB GPU, 32 GB DDR4 RAM, and Windows 11. All data will be stored on secure, password-protected systems within the HCM Laboratory.

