#### Real-time software latency assessment

Unity-side software latency was measured using a monotonic timestamp logger integrated into the application. For each QTM packet processed by Unity, the logger recorded the Unity-side packet reception time, EMG processing start and end times, and the time at which the corresponding visualization value was applied. Processing latency was calculated as the interval between processing start and end. Receive-to-visualization latency was calculated as the interval between Unity-side QTM packet reception and visualization update.

Across complete six-channel update cycles, receive-to-visualization latency had a median of 11.0 ms, a mean of 11.1 ± 5.1 ms, a 95th percentile of 18.2 ms, and a maximum of 35.3 ms. Unity-side EMG processing had a median latency of 0.0035 ms, a 95th percentile of 0.0050 ms, and a maximum of 0.3045 ms.

These results represent latency within the Unity software pipeline after each QTM packet was received.

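### The runtime EMG smoothing window is set as 20 updates rather than a duration, so feedback lag depends on an unstated update rate and is not part of the reported 11.0 ms latency

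*Protocol article*

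**What the plan says.** Under Runtime processing pipeline, the article gives the aim of the on-headset software: "Its purpose is to generate low-latency normalized EMG values for real-time visual feedback". Stage C describes how this is done. "The Unity application polls QTM for EMG data over Wi-Fi", and then "Unity computes RMS amplitude from the latest QTM analog sample packet, applies a 20-update rolling RMS window", before dividing by the MVIC reference. The resulting values drive all three displays, and "The feedback is rendered in either VR or MR mode according to group allocation". No polling rate, update rate or window duration is given, either overall or by arm or mode.

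The section Real-time software latency assessment reports that "receive-to-visualization latency had a median of 11.0 ms, a mean of 11.1 ± 5.1 ms, a 95th percentile of 18.2 ms", with a maximum of 35.3 ms. The interval is defined as starting when Unity receives a packet and ending when the display value is applied. The section closes with its scope: "These results represent latency within the Unity software pipeline after each QTM packet was received". The figures are pooled over arms and modes.

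By contrast, the offline pipeline (EMG signal processing) uses an RMS window of fixed length, 50 ms.

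**The concern.** A rolling window defined by a count has no fixed length in time. If updates arrive more slowly, the same 20 updates span a longer period, and the displayed value is both older and smoother. The window is therefore a property of the running system and not of the protocol.

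This matters because VR versus MR and avatar versus bar versus graph are the comparisons that the study is built to make, and the EMG feedback is the intervention. If one condition ran at a lower update rate than another, its participants would receive later and smoother feedback, and any effect of that would be read as an effect of immersion or display format. Randomizing the order of the modes would not remove a lag that belongs to a mode itself.

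The latency section is the only timing evidence in the article, and its timer cannot register this delay. It starts at the arrival of the newest packet, while the displayed value also draws on the 19 updates before it. That averaging takes place inside Unity, so it lies within the part of the system that the section sets out to describe.

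**Working it through.** **Inputs from the article**
- Window: 20 updates (Stage C).
- EMG sampling: "EMG will be sampled at 1926 Hz using the 20–450 Hz bandwidth setting" (Equipment and instruments).
- Camera rate: "Cameras will be synchronized at 300 Hz" (same section).
- Offline RMS window: 50 ms (EMG signal processing).
- Median receive-to-visualization latency: 11.0 ms (Real-time software latency assessment).

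**Input not in the article**
- Update rate r. Assumed range: 30 to 300 Hz, with the camera rate as the upper end.

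**The article's own figure.** The 11.0 ms is a measurement, and its log is not given, so it cannot be recomputed. The related timing inputs are consistent: 1/300 s = 3333 μs and half of that is 1667 μs, as stated for the synchronization pulse.

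**Formulas**
- Window length = 20/r.
- Mean age of the 20 updates relative to the newest = (0 + 1 + … + 19)/20 × 1/r = 19/(2r).

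| Assumed r | Window, 20/r | Mean age, 19/(2r) | Mean age ÷ 11.0 ms |
|---|---|---|---|
| 300 Hz | 66.7 ms | 31.7 ms | 2.9 |
| 90 Hz | 222.2 ms | 105.6 ms | 9.6 |
| 72 Hz | 277.8 ms | 131.9 ms | 12.0 |
| 60 Hz | 333.3 ms | 158.3 ms | 14.4 |
| 30 Hz | 666.7 ms | 316.7 ms | 28.8 |

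**Difference between two conditions, if there were one.** At 60 Hz against 90 Hz, the mean age differs by 158.3 − 105.6 = 52.7 ms from the rounded values (52.8 ms unrounded).

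**Comparison with the offline window.** Twenty updates last 50 ms only if r = 20/0.050 = 400 Hz, which is above the 300 Hz camera rate.

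**Response to a sudden change.** Mean age is a summary and not a pure shift in time. For an amplitude that jumps from zero to a plateau, the rolling RMS reaches half the plateau after 20 × 0.5² = 5 updates. When the amplitude drops back to zero, the RMS falls to half after 20 × (1 − 0.5²) = 15 updates. That is 16.7 and 50.0 ms at 300 Hz, and 83.3 and 250.0 ms at 60 Hz. The lag in showing relaxation is thus three times the lag in showing onset, and both scale with 1/r.

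**What the latency figures show.** EMG processing has a median of 0.0035 ms, against 11.0 ms from receipt to display, with SD 5.1 ms. Almost all of the reported interval is therefore something other than EMG computation. Waiting for a display update would be one explanation, but that is an inference.

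**The case against.** The strongest reply is that no confounding is shown. Both immersive arms use the same headset and the same Unity pipeline, and nothing in the article gives a rate by arm or mode or suggests that rates differ. A reader might infer that passthrough or the moving avatar slows the updates, but that is outside engineering knowledge and not in the document. The word update is not defined either. The latency section logs each processed packet, which also fits packet-driven updating. With a regular packet stream, 20 updates would then last the same time in every condition, and a constant delay would not bias either comparison. This stands: a difference between conditions is a possibility only.

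A reader might also infer that most of the EMG signal is discarded because each update uses the latest packet. Polling at 60 to 90 Hz would use 60/300 to 90/300, or 20 to 30%, of the samples, but only if each packet holds exactly one 300 Hz frame (1926/300 = 6.42 samples). The article does not give the contents or rate of the real-time packets, and a packet might hold everything since the previous poll. The displayed value also pools 20 updates and not one. Sample loss is therefore not established.

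A third tempting reading is that the 11.0 ms misstates how current the displayed signal is. The section defines its interval and limits its scope openly, and it never presents the figure as the age of the signal. It is incomplete and not false.

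Two further replies are fair. Objective outcomes are computed offline from the raw recordings with a fixed 50 ms window, so their measurement is untouched, and the article offers no evidence on whether tens of milliseconds would change performance in these exercises. The source code is also said to be available and may contain rate settings. But the rule printed in the article is itself stated in a rate-dependent unit, so this is more than an omitted detail.

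**Conclusion.** The point holds in a limited form. The article fixes the smoothing of the delivered feedback in a unit whose duration depends on a rate that it neither states nor locks. For assumed rates of 300 to 60 Hz, the window runs from about 67 to 333 ms and the mean lag from about 32 to 158 ms, which is 2.9 to 14.4 times the reported median of 11.0 ms. The reported latency does not contain this delay and is not broken down by arm or mode, so it cannot show that the conditions are alike in feedback timing.

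The consequence is an avoidable possible confound in the VR/MR and visualization-mode comparisons. Whether it occurs depends on update rates that the article does not give; if all conditions share one stable rate, the delay is common to them and does not confound. The issue concerns the intervention as delivered and leaves the offline outcome computation sound. It is worth correcting before full data collection, because a lag tied to a condition could not be separated from that condition afterwards.

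**What to change.** - Define the runtime RMS window in Stage C as a fixed duration in milliseconds, computed from packet timestamps and identical in VR, MR and all three modes.
- Make sure that all analog samples received since the last poll enter the window, and state what a packet contains.
- Log the achieved update rate for every block with the existing timestamp logger, so that equality across arms and modes can be checked.
- In Real-time software latency assessment, report the window delay beside the 11.0 ms figure, and give both by VR/MR and by mode.

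The cost is a small software change and a repeat of the latency check, with a logger that already exists. The drawback is that the reported latency will look less favourable.

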#### Post-session processing pipeline

Following each session, raw QTM exports containing 3D marker trajectories and analog EMG channels are processed offline in Python (v3.11) using SciPy and NumPy to compute the objective outcome measures. Questionnaire outcomes are scored separately according to their standard scoring procedures. The offline pipeline applies higher-precision processing than the runtime pipeline because it is not constrained by real-time latency.

##### EMG signal processing

The following steps are applied to each EMG channel for every trial:1.**DC offset removal:** mean subtraction per channel and trial.2.**Band-pass filtering:** 4th-order zero-phase Butterworth filter, 20–450 Hz.3.**Notch filtering:** 2nd-order IIR notch filter at 50 Hz to reduce power-line interference.4.**Full-wave rectification:** absolute value of the filtered signal.5.**RMS envelope extraction:** the RMS envelope is computed using a sliding window as:$$\text{RMS}\left[n\right]=\sqrt{\frac{1}{N}\sum_{i=0}^{N-1}x^{2}\left[n-i\right]}$$where n is the current sample index, i is the sample offset within the sliding window, x is the filtered EMG signal, and N is the number of samples in the RMS window. A 50 ms RMS window is used for exercise trials for smoother visualization.

**6. MVIC normalization:** exercise EMG is expressed as a percentage of maximum voluntary isometric contraction (%MVIC) using the corresponding per-muscle, per-side MVIC reference:

$\%\text{MVIC}\left[n\right]=\frac{\text{RM}S_{\text{exercise}}\left[n\right]}{\text{RM}S_{\text{MVIC},\text{peak}}}\times \;100$where n is the current sample index, $\text{RM}S_{\text{exercise}}\left[n\right]\;$is the exercise RMS value at sample n, and $\text{RM}S_{\text{MVIC},\text{peak}}$ is the peak RMS value obtained from the central 5 s of the highest-amplitude MVIC trial.**7. Feature extraction:** mean %MVIC, peak %MVIC, time-to-peak activation, and activation duration using a 10% MVIC onset/offset threshold.

##### Kinematic processing

Raw 3D marker trajectories are processed using the Qualisys Sports Marker Set segment definitions. The pipeline computes shoulder and elbow joint angles, joint-angle accuracy, range of motion, angular velocity, movement smoothness, and compensatory motion. Compensatory movement is quantified using trunk displacement and contralateral limb excursion during unilateral exercises.

#### Temporal alignment and repetition segmentation

EMG and kinematic data are aligned using the common hardware timing reference established by the TTL synchronization signal. Individual repetitions are segmented using kinematic event detection based on local minima and maxima of the primary joint-angle trajectory, identified from zero-crossings of the smoothed angular velocity signal.

#### Real-time software latency assessment

Unity-side software latency was measured using a monotonic timestamp logger integrated into the application. For each QTM packet processed by Unity, the logger recorded the Unity-side packet reception time, EMG processing start and end times, and the time at which the corresponding visualization value was applied. Processing latency was calculated as the interval between processing start and end. Receive-to-visualization latency was calculated as the interval between Unity-side QTM packet reception and visualization update.

Across complete six-channel update cycles, receive-to-visualization latency had a median of 11.0 ms, a mean of 11.1 ± 5.1 ms, a 95th percentile of 18.2 ms, and a maximum of 35.3 ms. Unity-side EMG processing had a median latency of 0.0035 ms, a 95th percentile of 0.0050 ms, and a maximum of 0.3045 ms.

These results represent latency within the Unity software pipeline after each QTM packet was received.

## Limitations

•The single-session design precludes assessment of motor learning effects, skill retention, and long-term adherence outcomes that are critical for evaluating the clinical utility of immersive rehabilitation systems.•The exclusive focus on healthy young adults may limit the generalizability of findings to clinical populations with shoulder pathology, older adults, or individuals with physical or cognitive impairments relevant to rehabilitation.•Because participants in the VR and MR groups experience all three visualization modes in a single session, learning, fatigue, or carryover effects between visualization blocks may influence performance. Randomized visualization order and rest intervals are used to reduce these effects, but they cannot be fully eliminated.

## Supplementary material and/or additional information

The source code and implementation materials supporting this protocol are available at:

Unity XR application: https://github.com/[name]/HCM_EMG_XR

MVIC Server: https://github.com/[name]/HCM_EMG_XR/tree/main/MVIC_Server

## Data Availability

The data that has been used is confidential.
